## Abstract

**Background:**

Family caregiver interventions are essential to support dementia caregiving. However, such interventions are typically complex and consist of multiple components. Existing evidence rarely delineates the effectiveness and interactions between individual components. To optimise intervention, we adopt the multiphase optimisation strategy (MOST) to test the implementation fidelity and determine the effect of each component and the interactions between each component and the corresponding outcome.

**Methods:**

A prospective, assessor-blinded, randomised clinical trial with fractional factorial design using the MOST principle. Two hundred fifty family dementia caregivers will be randomised to one of 16 experimental conditions in a fractional factorial design involving six intervention components: (1) dementia and caregiving education; (2) self-care skills; (3) behavioural symptom management; (4) behavioural activation; (5) modified mindfulness-based cognitive therapy; and (6) support group. The first one is the core component, and the five remaining will be examined. Physical health, caregiver burden, stress, psychological well-being, anxiety and depressive symptoms, and social support will be assessed over the 12-month study period. Following the intention-to-treat principle, linear mixed models and regression analyses will be used to examine the specific effect of the five components and their two-way interactions to propose the most effective combination.

**Discussion:**

This is the first study adopting the multiphase optimisation strategy to identify the most active and engaging components of a psychological intervention for caregivers of patients with dementia. In view that dementia caregiver interventions are increasingly diversified and complex, such knowledge is important to maximise the intervention efficacy and allow the intervention to be implemented within an efficient timeframe and dosage. The optimisation of caregiver support interventions is critical to enhance the health outcomes of caregivers and care recipients, thereby, delaying possible institutionalisation and reducing the costs of long-term dementia care.

**Trial registration:**

This study was retrospectively registered in the WHO Primary Registry – Chinese Clinical Trials Registry (ChiCTR2300071235). (Protocol date 30/10/2020; version identifier 2020–2021-0045). Registered on 9 May, 2023.

**Reporting method:**

SPIRIT guideline was followed.

**Patient or public contribution:**

No patient or public involvement.

**Supplementary Information:**

The online version contains supplementary material available at 10.1186/s13063-023-07801-3.

## Main paper

### Introduction

Dementia is an impending healthcare crisis that affects more than 55 million individuals worldwide. With the ageing population, this number is expected to reach approximately 78 million by 2030 and 139 million by 2050 [1]. The global financial burden of dementia is estimated to be USD 1.3 trillion and may reach USD 2.8 trillion by 2030. Dementia is a progressively degenerating disease that causes multiple cognitive deterioration, which results in disability, dependence, institutionalisation and mortality. Long-term care of patients with dementia is mostly provided by family caregivers, who provide unpaid or informal attention and play an essential role for the persons they are taking care of and for the overall healthcare system. Family dementia caregivers are more stressed, suffer more serious anxiety and depressive symptoms and are at higher risk of cardiovascular diseases than non-dementia caregivers [2]. These over-burdened caregivers are more likely to give up their caregiver role by institutionalisation of their care recipient [3]. All of these factors are projected to significantly increase the costs of healthcare and long-term care in the future. Therefore, effective interventions should be designed to reduce the negative effects of caregiving on family dementia caregivers.

A recent systematic review and meta-analysis compared the effects of 131 randomised controlled trials (RCTs) for dementia caregivers with community-dwelling care recipients; the result showed that multicomponent interventions had the most significant effect among nonpharmacological interventions on reducing the burdens on family dementia caregivers, decreasing their stress levels and enhancing their subjective well-being [4]. An earlier meta-analysis reported that multicomponent interventions are effective in delaying or preventing the institutionalisation of people with dementia [5]. Despite the favourable outcomes of multicomponent interventions, the effectiveness of individual components is concealed with the black box approach in traditional RCTs. Caregiving support interventions are often complex and consist of multiple components in variable combinations. For example, an intervention may include components, such as education on dementia and caregiving education, self-care skills, behavioural symptom management, stress management and support group. Traditional RCTs have only examined the effectiveness of various combinations of interventions as a package. The effectiveness of individual components of a multicomponent intervention has been rarely tested. As such, studies of broadly conceived family caregiver programmes consisting of different components have produced highly varied results in terms of effect size, which ranges from small to medium [4]. Components and behavioural skills that can effectively alleviate caregiving burden and enhance psychosocial outcomes among dementia family caregivers and to whom they are suitable for remain to be identified.

The multiphase optimisation strategy (MOST) developed by Collins and her colleagues [6] is an innovative approach for examining which components of a multicomponent intervention are effective in achieving a particular outcome, singly and in combination with one another. The value of MOST has been established in recent research in several areas, including cessation of smoking, promotion of physical activity, reducing obesity, reducing alcohol use and unsafe sex and conducting education interventions [7]. However, to our knowledge, MOST has not been applied in gerontology, making our proposed study the first of its kind. MOST consists of three stages: (1) preparation to conduct an optimisation trial, (2) optimisation to reveal what constitutes an optimised intervention and (3) evaluation of the optimised intervention relative to an established intervention in an RCT. In this study, we will focus only on the preparation and optimisation phases due to resource and time constraints.

In the preparation phase, we will use six core psychoeducational components, namely, (1) education on dementia and caregiving, (2) self-care skills, (3) behavioural symptom management, (4) behavioural activation, (5) modified mindfulness-based cognitive therapy and (6) social support. Components 1 to 4 and 6 were adapted from the ‘Resources for Enhancing Alzheimer’s Caregiver Health’ (REACH) intervention [8–10], which is one of the most studied multicomponent interventions for informal dementia caregivers. Two multicomponent intervention studies of REACH that considered cultural perspective in caregiving [11] were conducted in Hong Kong and reported positive preliminary findings. In the 2010 study [9], Au adapted and evaluated the multicomponent intervention called Coping with Caregiving, which is one version of REACH; they found that the intervention enhanced caregiving self-efficacy and effective coping strategies. In the 2015 study [10], Cheung conducted an implementation study of the translated version of REACH II by using a quasi-experimental single-group pre − post treatment design. They found that it had significant effects on the perception of positive aspects of caregiving, reduction in depressive symptoms, subjective burden, bother and caregiving risks among caregivers and abatement in behavioural problems among care recipients. Promises in reach and adoption were demonstrated by the participation of 85 interventionists from 11 non-governmental organisations across 18 districts and 243 caregivers of various demographic characteristics. In a 2020 meta-analysis [4], multicomponent interventions for dementia caregivers had limited positive effect on depressive symptoms. By contrast, mindfulness-based interventions significantly reduced anxiety and depressive symptoms [4, 12–15]. Hence, this proposed study will incorporate the modified mindfulness-based cognitive therapy, which has been tested effectively among dementia caregivers, as a stress management component [16, 17].

Following the MOST framework, we will select the treatment components carefully to ensure that they are conceptually and operationally distinct from one another, so each component can be evaluated independently. However, we do not assume that the treatment components do not interact. Interaction effects may exist between individual components and influence primary outcomes. For example, during support group sessions, caregivers may exchange skills and information on managing the behavioural symptoms of care recipients by sharing and discussion; as such, the caregivers may build strong bonds and a sense of social support. As a result, behavioural symptom management component may moderate and strengthen the relationship between the support group component and perceived social support. In this regard, social support had a significant effect only when incorporated in multicomponent interventions instead of other domain-specific interventions [18]. Therefore, in the optimisation phase, we will use a factorial approach with effect coding to concurrently test the main effects of individual components and their interaction effects. All experimental conditions will involve education on dementia and caregiving as the core component, since it has been identified as the most ubiquitous component for caregiver support programmes as well as its ease of implementation. This factional factorial design will reduce the total number of conditions from 32 to 16, which retains the benefits of a factorial design whilst allowing a more logistically manageable and feasible study.

Another major limitation of studies on multicomponent interventions is that researchers often omit to report whether components have been implemented with fidelity; thus, the implementation fidelity of individual components remains unknown [19]. Assessment of implementation fidelity is an important first step in determining the effectiveness of a treatment component. Moreover, to our knowledge, no previous study has examined the underlying mechanism of individual components of multicomponent interventions. The factorial design of single intervention components will enable us to determine not only which components are the most strongly associated with changes in primary outcomes but also the fidelity of the implementation of each component, the components that lead to improvements in corresponding proximal outcomes (i.e. the goal of the component) and whether the proximal outcomes mediate the effects of their corresponding components on primary outcomes (i.e. understand the underlying mechanism of each component).

Multicomponent interventions can be tailored to meet the specific needs of individual caregivers given the variability inherent in caregiving situations [8]. Specific treatment modules or strategies and techniques may be applied according to the risk profiles of caregivers to provide personalised support. However, whether such matching between the risk profiles of caregivers and individual components works better than a one-size-fits-all approach remains unknown because the relative efficacy of a specific component on a specific outcome has yet to be examined systematically. Hence, this study will also determine the moderating effects of the baseline scores of primary outcome measures in the relationship between intervention components and primary outcomes.

Although theoretical and empirical evidence suggests the positive effects of multicomponent interventions, a limited number of dementia caregiving support interventions have looked into the “black box” to understand which intervention components work or do not work, and how they work. To optimise the efficacy and scalability of multicomponent interventions, investigations should cover implementation fidelity, the main effect of individual components and their interactions and the underlying mediating/moderating mechanism. This study aims to address these research gaps. The findings will provide a wider repertoire of evidence-based personalised multicomponent interventions to support dementia caregivers.

#### Objectives

This study aims to:determine the implementation fidelity of each intervention component,assess the effect of each component on corresponding proximal outcomes,examine the effect of each component on primary outcomes (e.g. depression, burden),determine if the proximal outcomes of each component mediate the components’ effects on primary outcomes,determine the interaction effect between components on their proximal and primary outcomes anddetermine the moderating effect of the baseline scores of primary outcomes in the relationship between each intervention component and the corresponding outcome.

The hypotheses to be tested are as follows:The implementation fidelity of all six components is equally high.Components 2 (self-care skills), 3 (behavioural symptom management), 4 (behavioural activation), 5 (modified mindfulness-based cognitive therapy) and 6 (support group) will have significant effects on proximal outcomes, namely, self-care, dementia caregiving strategy, engagement in pleasurable activity, mindfulness and satisfaction with support group, respectively.Components 2–6 will have a stronger effect on their corresponding primary outcomes, namely, physical health status, stress/burden, psychological well-being, anxiety/depressive symptoms and social support, respectively, than the other components.Self-care, dementia caregiving strategy, engagement in pleasurable activity, mindfulness and satisfaction with support group mediate the relationship between component 2 and physical health status, between component 3 and stress/caregiving burden, between component 4 and psychological well-being, between component 5 and anxiety/depressive symptoms and between component 6 and social support, respectively.Component 3 moderates the relationship between component 6 and social support.The baseline scores of physical health status, stress/burden, psychological well-being, anxiety/depressive symptoms and social support moderate the effects of components 2–6 on changes in scores between the baseline and follow-up assessments of the corresponding outcomes.

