#### Trial design

This study adopts a prospective, assessor-blinded, randomised controlled trial with fractional factorial design by using the MOST principles to evaluate the effects of the five individual components and their two-way interactions (including self-care skills, behavioural problem management, behavioural activation, mindfulness yoga and support group; Table 1). A complete factorial experiment of the five factors would have 2^5^ = 32 experimental conditions (ECs). To conserve resources and reduce logistical complexity, we select a 25–1 fractional factorial design and decrease the number of ECs from 32 to 16 [20]. Our fractional factorial design is made up of a strategically selected subset of 32 ECs based on prioritising the estimation of intervention component main effects and two-way interactions [21]. All the included ECs are listed in Table 1. The study contains a subset of ECs, so the participants will not be randomised into a usual care/control group but every EC can be served as a control condition under different circumstances to test the effect of each component. For example, the effect of component 2 on primary outcomes could be examined through the comparison of participants in EC1 to EC8 and those in EC9 to EC16. In addition, the study assumes the presence of overlapping components within the 16 ECs. These overlaps will be recognised and carefully measured through fidelity monitoring. This study will conform with the Declaration of Helsinki.

**Table 1 Tab1:** Experimental conditions of the fractional factorial RCT

	Component					
Experimental condition	1	2	3	4	5	6
1	Yes	Yes	Yes	Yes	Yes	Yes
2	Yes	Yes	Yes	Yes	No	No
3	Yes	Yes	Yes	No	Yes	No
4	Yes	Yes	Yes	No	No	Yes
5	Yes	Yes	No	Yes	Yes	No
6	Yes	Yes	No	Yes	No	Yes
7	Yes	Yes	No	No	Yes	Yes
8	Yes	Yes	No	No	No	No
9	Yes	No	Yes	Yes	Yes	No
10	Yes	No	Yes	Yes	No	Yes
11	Yes	No	Yes	No	Yes	Yes
12	Yes	No	Yes	No	No	No
13	Yes	No	No	Yes	Yes	Yes
14	Yes	No	No	Yes	No	No
15	Yes	No	No	No	Yes	No
16	Yes	No	No	No	No	Yes

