#### Proximal outcomes

*Self-care* will be measured by the 14-item self-care subscale in Risk Appraisal Measure (RAM-SC) [42, 43]. The subscale illustrates the unique risk profile of caregivers in terms of self-care. A high score indicates a low risk of caregivers.

*Caregiving strategies* will be measured by the 34-item Dementia Management Strategies Scale (DMSS) [42, 43]. The scale uses a 5-point Likert scale and consists of three domains, namely, criticism, encouragement and active management. The Cronbach’s alpha of the three subscales ranges from 0.86 to 0.90 [42, 43].

*Engagement in pleasurable activities* will be measured by recording the frequency (times per week) and duration (minutes in each time) of each engagement in the past 2 weeks.

*Mindfulness* will be measured by the 20-item version of the Five Facet Mindfulness Questionnaire (FFMQ) [44]. Using a 5-point Likert scale, it measures five facets of mindfulness, namely, observing (4 items), describing (4 items), acting with awareness (4 items), nonjudging to inner experience (4 items) and non-reacting to inner experience (4 items). A high score reflects a high level of mindfulness. The Cronbach’s alpha values are 0.83 in the community sample and 0.80 in the clinical sample [44].

*Social support* will be measured by the 12-item Multidimensional Scale of Perceived Social Support (MSPSS) [45]. The scale uses a 7-point Likert scale and consists of three sources of support: family, friends and significant other. The Cronbach’s alpha of the three subscales ranges from 0.85 to 0.91. [46].

*Satisfaction with the support group* will be measured on a 7-item scale during the post-intervention. Participants will report their satisfaction with specific components and quality of service [46].

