#### Data analysis

This study will adopt the principle of intention-to-treat for data analysis of the individual intervention components (components 2–6). The main objective is to examine the level of significance of each factor on proximal and primary outcomes by using linear mixed models at three time points (T0, T1 and T2). Linear mixed regression models account for repeated measures within participants and handle missing data using maximum likelihood estimation in a longitudinal dataset without needing multiple imputations [51]. The pre − post within group difference will also be investigated (i.e. T1 vs. T0 and T2 vs. T0). On the one hand, the across time difference of each component can be viewed as the main effect. On the other hand, such effect will be modelled as components by time interactions, with T2 outcome as the primary endpoint. The study will also include the analysis for two-way interactions between components (i.e. factor 3 by factor 6 by time interaction).

The examination of moderation and mediation effects of significance will follow the guidelines established by MacKinnon and Luecken [52]. To detect the underlying mechanism of components, the study will test for fit of the mediation model. The relationship path between each component and their respective primary outcomes will be established. The pathway between the components and proximal outcomes and between the proximal and primary outcomes will be investigated. The relationship between the components and primary outcomes mediated by the proximal outcomes will be investigated. When testing the fit of the moderation model, the relationship between each component and the change of primary outcome will be examined. Afterwards, the strength and direction of the relationship will be tested again accounting for the effects of the baseline primary outcomes. The moderation models will be used to identify the interaction effects of the matching risk profiles of caregivers with specific components. The moderating effects of the matching profiles with components have never been explored in previous studies.

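### For component 6 only, Hypotheses 2 and 4 cannot be tested as written: satisfaction with the support group has no baseline and is undefined in the 8 of 16 conditions without a group

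*Protocol article*

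**What the plan says.** The Objectives section pairs each of components 2 to 6 with one proximal outcome. In Hypothesis 2 the series ends "engagement in pleasurable activity, mindfulness and satisfaction with support group, respectively", so component 6 is expected to affect satisfaction with the support group. Hypothesis 4 names the same variables as mediators, ending "between component 5 and anxiety/depressive symptoms and between component 6 and social support, respectively".

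Under Proximal outcomes, satisfaction with the support group "will be measured on a 7-item scale during the post-intervention". The content of the scale is described this way: "Participants will report their satisfaction with specific components and quality of service". The same section lists a further proximal measure, social support, which "will be measured by the 12-item Multidimensional Scale of Perceived Social Support (MSPSS"). Neither Hypothesis 2 nor Hypothesis 4 mentions it.

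The Trial design section defines a component's effect as a comparison of conditions with and without it. Its example, for component 2, sets the first eight conditions against the last eight. The Data analysis section applies linear mixed models at T0, T1 and T2 to proximal and primary outcomes alike and expresses effects as component-by-time interactions. On mechanism it adds: "The relationship between the components and primary outcomes mediated by the proximal outcomes will be investigated".

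**The concern.** A component's effect on a variable can be estimated only if the variable exists both with and without the component. Satisfaction with a support group exists only for people who were offered one. Assignment to component 6 and availability of its proximal outcome therefore coincide. The values for the other participants are undefined rather than missing, so likelihood-based handling of missing data does not supply them.

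Mechanism is a stated aim of the trial, and the loss falls on it. The likely fallback is to correlate satisfaction with social support among those who had a group. That is a non-randomised association within one level of the factor, and it could be reported as mediation although it says nothing about the effect of component 6.

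**Working it through.** **Inputs**

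- Table 1 ("All the included ECs are listed in Table 1"): component 6 is Yes in EC1, 4, 6, 7, 10, 11, 13 and 16, and No in EC2, 3, 5, 8, 9, 12, 14 and 15.
- Sample size estimation: 250 recruited, 200 evaluable after 20% attrition, d = 0.40, 80% power, two-tailed.
- Proximal outcomes: satisfaction is measured post-intervention only.
- Data analysis: mixed model over T0, T1 and T2, with effects as component-by-time interactions.

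**The plan's own figure**

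- With two-sided alpha of 0.05, n per level = 2 × (1.960 + 0.842)² / 0.40² = 2 × 7.85 / 0.16 = 98.1, so 99 per level (198 in total). The t-test version gives 99.1, so 100 per level (200 in total).
- Power with 100 per level is 0.807 (normal) or 0.804 (t-test).
- Recruitment: 200 / (1 − 0.20) = 250.

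The stated 200 and 250 are reproduced. The article prints alpha as 0.5, which would need only 29 per level, so 0.05 is assumed here. That misprint does not affect this point.

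**Component 6 in the full design**

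With Yes = +1 and No = −1, the component 6 column of Table 1 sums to zero and is orthogonal to the columns of components 2 to 5. Assuming equal allocation:

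- randomised: 250 × 8/16 = 125 against 125;
- evaluable: 200 × 8/16 = 100 against 100.

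Any outcome measured in all 16 conditions therefore gives a proper contrast for component 6.

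**Component 6 on satisfaction with the group**

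The quantity in Hypothesis 2, and the first path in Hypothesis 4, is

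a = E[satisfaction | component 6 = Yes] − E[satisfaction | component 6 = No].

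The second term is undefined. Among the 8 conditions that can supply a score, the component 6 column is constant at +1, its variance is 0, and the matrix [intercept, component 6] has rank 1 instead of 2. The comparison is about 125 against 0 randomised, or 100 against 0 evaluable. No sample size makes a estimable, so the indirect effect a × b (b being the path from mediator to outcome) is not estimable either.

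**The planned model**

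The component-by-time effect for this variable would be

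(change from T0 | Yes) − (change from T0 | No).

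There is no T0 value in either level, so neither change can be formed, quite apart from the missing comparison level.

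**What is left**

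Four of five component–proximal pairs in Hypotheses 2 and 4 (components 2 to 5) do not use this variable. Hypothesis 3 (component 6 on social support), Hypothesis 5 (component 3 by component 6) and Hypothesis 6 (baseline moderation) use the primary outcome MOS-SSS for component 6, which can be measured in all 16 conditions.

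**The case against.** The strongest objection is that little of importance depends on this variable. The Discussion gives the primary objective as the effect of each component on its corresponding primary outcome and the choice of the best combination. Proximal and mediation analyses are not part of that statement. This stands, and it limits the severity.

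A second objection is that the article already lists a usable measure. MSPSS is a proximal outcome, and Figure 3, which is said to list all proximal outcomes, is not shown and may pair it with component 6. That makes the repair cheap. It does not change Hypotheses 2 and 4, which name satisfaction.

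A third is that the post-intervention satisfaction questionnaire is not expressly restricted to group attendees, so participants without a group might return scores on service quality. They might, but such a score is not satisfaction with the support group, and it still has no baseline.

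A reader might infer that Hypotheses 2 and 4 fail altogether, or that component 6 cannot be evaluated in this trial. The protocol supports neither. The other four pairs do not use this variable, and the primary-outcome tests of component 6 do not depend on it.

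A reader might also infer that substituting MSPSS repairs both hypotheses equally. It does not. MSPSS and MOS-SSS both measure perceived social support, so a significant indirect effect could reflect overlap of construct and say little about mechanism.

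**Conclusion.** The point holds for component 6 only. Its named proximal outcome and mediator is undefined in 8 of 16 conditions and has no baseline, so one of five proximal-effect tests and one of five mediation tests cannot be carried out as written. The problem is identification, not power. An analysis plan could not cure it without changing the named variable.

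It should be fixed, but it is not critical, because no primary-outcome test is affected. The figure of about 125 of 250 participants rests on equal allocation across the 16 conditions, which the article does not state. The count of 8 of 16 conditions does not depend on that.

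**What to change.** - **Hypothesis 2:** name MSPSS as the proximal outcome of component 6, and analyse component 6 Yes against No across all 16 conditions with the planned mixed model. This restores about 100 against 100 evaluable participants, hence about 80% power if d = 0.40 is taken to apply to MSPSS. Collection at T0, T1 and T2 is inferred from the general schedule under Data collection procedures and Data analysis, because the schedule figure is not shown. It should be confirmed.
- **Hypothesis 4:** remove satisfaction as the mediator for component 6. If mediation through MSPSS is still wanted (for example T1 MSPSS and T2 MOS-SSS, each adjusted for baseline), label it exploratory and give the overlap between the two scales as the reason.
- **Satisfaction:** report it descriptively among participants assigned a support group, and do not present its correlation with social support as mediation.
- **Record:** Trial status gives the end of recruitment as Dec 31, 2022 and the last follow-up as Nov 30, 2023. Replacing a named variable at that stage changes a hypothesis, so it needs a dated, justified amendment made before outcome data are examined.

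The cost is hypothesis and analysis wording plus the amendment. No new data are needed if MSPSS was collected on the general schedule.

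### Hypothesis 3 ranks each component above the others on its matched outcome, but the stated analysis and power test each effect only against zero

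*Protocol article*

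**What the plan says.** Under Objectives, the protocol article lists the hypotheses to be tested. The third (Hypothesis 3 below) is the only one about component main effects on the primary outcomes, and it is comparative. Components 2 to 6 "will have a stronger effect on their corresponding primary outcomes", and the sentence ends "anxiety/depressive symptoms and social support, respectively, than the other components".

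The Data analysis section fixes a different question: "The main objective is to examine the level of significance of each factor on proximal and primary outcomes by using linear mixed models". It adds that "such effect will be modelled as components by time interactions, with T2 outcome as the primary endpoint". The other listed analyses are pre-post differences, two-way interactions between components, mediation, and moderation by baseline score.

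The Introduction states that "we will use a factorial approach with effect coding to concurrently test the main effects of individual components and their interaction effects", so the components enter one model together.

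The Sample size estimation section gives 200 analysable participants for 80% power to detect a main or interaction effect of 0.40, and 250 recruited to allow for 20% attrition. The Discussion restates the primary objective without a comparison: to estimate each component's effect on its corresponding outcome.

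**The concern.** Hypothesis 3 is about the difference between two effects on the same outcome. Each component-by-time term is tested against zero, which is a different question. The remaining analyses do not fill the gap. An interaction asks whether one component's effect depends on another's presence, not which effect is larger. Pre-post differences, mediation and baseline moderation do not compare components either.

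An analyst who follows the text has only significant and non-significant results to set beside Hypothesis 3. Such a pattern arises easily when the true effects are equal. The trial could then report that a component works best on its own outcome with no test of that claim. The only power figure in the article also gives no idea how imprecise the comparison is.

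**Working it through.** **Inputs.** From Sample size estimation: effect 0.40 SD, N = 200, 80% power, two-tailed, 20% attrition. From Table 1: the 16 conditions. Alpha is taken as 0.05, because the printed 0.5 does not reproduce the stated N (it would need 58 participants). Equal allocation is assumed. The true effects and differences used below, other than 0.40, are assumptions; the article gives none.

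**The plan's own figure.** Two-sided 0.05, 80% power, difference 0.40 SD: 99 per level, 198 in total. Power at 100 per level is 80.7%. Attrition: 200 / 0.80 = 250. The stated sample size reproduces for a single component, present versus absent.

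**Structure of Table 1.** With yes = +1 and no = −1, the five component columns are mutually orthogonal, and the product of the five codes is +1 in every row. Main-effect estimates are therefore uncorrelated under equal allocation.

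**Standard errors at N = 200, in SD units.**
- One main effect: 2/√200 = 0.141.
- Difference between two main effects: 0.141 × √2 = 0.200.

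A direct check gives the same value. Component 2's effect minus component 3's reduces to comparing the conditions with 2 but not 3 (EC5 to EC8) with those with 3 but not 2 (EC9 to EC12). That is 50 against 50 participants: √(1/50 + 1/50) = 0.200.

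**Power for one pairwise contrast, two-sided 0.05.**

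| True difference (SD) | Power, N = 200 | With Bonferroni over 4 | N for 80% power |
|---|---|---|---|
| 0.40 | 52% | 31% | 396 |
| 0.30 | 32% | 16% | 700 |
| 0.20 | 17% | 7% | 1572 |

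The detectable difference at 80% power is (1.96 + 0.84) × 0.200 = 0.56 SD. With all 250 retained the standard error is 0.179, and power for 0.40 is 61%.

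**Own component above all four others.** If every one of the four contrasts must be significant at N = 200, simulation gives 21% when the own effect is 0.40 and the others are 0, and 2.4% when the others are 0.20.

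**What separate tests show when two true effects are equal.** With single-test power p, exactly one of the two is significant with probability 2p(1 − p):
- 0.20 SD: p = 0.293, giving 41%.
- 0.30 SD: p = 0.564, giving 2 × 0.564 × 0.436 = 49%.
- 0.40 SD: p = 0.807, giving 31%.

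These figures ignore any gain from baseline and repeated measures, since the article gives no correlation. Such a gain would shrink both standard errors; the ratio of √2 between them would remain.

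**The case against.** The strongest reply is that the analysis fits the objective. The third objective and the Discussion speak of each component's effect on primary outcomes, with no comparison, and the sample size is right for that. This stands. The sample size is not in error, and the article claims no power for comparisons. The mismatch lies between Hypothesis 3 and the analysis.

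A second reply is that the contrast is detail for an analysis plan. The Introduction's concurrent, effect-coded model yields all five effects on one scale, so any contrast is available from the same fit. It follows that the components are not analysed in separate models. But the article does more than omit detail: it states a comparative hypothesis and then fixes its main test and power on another question.

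Three stronger readings are tempting, and the article does not support them.
- A reader might infer that Hypothesis 3 will be declared from a pattern of p-values, and attach an error rate. No decision rule is stated, and the rate depends heavily on the rule. With all five effects equal at 0.30 SD, own significant and at least one other not occurs 51% of the time (0.564 × (1 − 0.564⁴)). Own significant and all four others not occurs about 2% (0.564 × 0.436⁴).
- A reader might infer that matching components to caregivers rests on Hypothesis 3. The Introduction and Data analysis assign matching to moderation by baseline scores.
- A reader might think that own effect minus the mean of the other four tests the hypothesis. It is more precise (SE 0.141 × √1.25 = 0.158; 72% power for 0.40), but it can favour the own component when another is stronger. With own 0.40, one other 0.50 and the rest 0, the contrast is 0.40 − 0.125 = 0.275 and is significant about 41% of the time.

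**Conclusion.** The concern holds in a limited form. Hypothesis 3 claims that one effect exceeds the others, no stated analysis compares effects, and the power statement covers a single effect. At N = 200 each comparison has a standard error of about 0.20 SD, about 52% power for a 0.40 SD difference, and a detectable difference of about 0.56 SD. This assumes alpha 0.05, equal allocation, and no gain from baseline or repeated measures. The 49% figure illustrates why separate tests cannot show that one effect is stronger. It assumes two equal effects of 0.30 SD and is not an error rate of a rule the article states. The estimates of each component's own effect, and the sample size for them, are unaffected.

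**What to change.** Before the analysis, do one of two things.

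1. **Test the hypothesis as worded.** In the same effect-coded mixed model, for each primary outcome, pre-specify four contrasts at T2, the endpoint named in Data analysis: the own component's effect minus each of the other four, signed so that positive means benefit, with 95% confidence intervals. Call Hypothesis 3 supported for an outcome only if all four intervals lie above zero. Requiring all four needs no further multiplicity adjustment within an outcome; a claim from any single contrast would. State the precision and power given above. The Discussion words the primary objective as within 6 months, so the time point should be confirmed at the same time.

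2. **Reword the hypothesis.** State that each component has an effect on its matched outcome, in line with the Discussion, and draw no conclusion from the separate tests that one component is stronger than another.

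The first costs a few contrast statements per model and a less favourable power figure. The second costs the comparative claim. Neither changes the design. Recruitment closed on 31 December 2022 according to Trial status, so a larger sample is not an available remedy.
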